### For oncologic patients

#### Quality of surgical specimen

All surgical specimens will be photographed according to an agreed protocol. The specimen will be placed on a clean surface before the bowel is opened. The mesentery will be spread out for visualization. The main vascular branches as well as the tumor will be pointed out with an instrument (e.g., Crile). The specimen will be evaluated by an independent, blinded specialist in gastroenterological surgery. To classify a right-sided colon specimen, the Benz classification will be used [20]. Left-sided specimens will be classified according to previously agreed criteria including the level of vascular ligation and quality of mesentery (Additional file 3).

#### Pathologic report and TNM classification

The number of lymph nodes (both the number of retrieved lymph nodes and nodes affected by cancer will be recorded)Site of any metastases

#### Overall survival (OS)

OS is defined as the time (years) from initial cancer treatment to death for any reason.

#### Cancer-specific survival (CSS):

CSS is defined as the time (years) from initial cancer treatment to death caused by the same cancer.

#### Disease-free survival (DFS)

DFS is defined as the time (years) from initial cancer treatment to recurrence of the cancer or death for any reason.

### Pre-intervention data

Diagnosis and reason for the emergency operation (obstruction, perforation, ischemia etc.)Age, sex, BMI, ASA classification, co-morbidity according to the Charlson comorbidity index [28], previous abdominal operations, and medication use of anticoagulants, oral cortisone, or immunosuppressantsNeed for ICU treatment preoperatively (yes/no)

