### Outcomes

The main endpoint of the study will be 30-day postoperative morbidity, which will be evaluated from the Comprehensive Complication Index (CCI) of all patients. CCI is the sum of all complications weighted on with their severity based on the Clavien-Dindo classification (CCI = √(*wC* + *wC*2 + … + *wCx*)/2) and has values ranging from 0 to 100 [24].

The secondary endpoints of the study are as follows.

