### Sample size

Sample size calculations will be based on previous studies, which report 48.3% 30-day postoperative morbidity after open surgery and 27.8% after laparoscopy [22]. The aim of the study is to show that postoperative morbidity is lower after laparoscopic surgery. Assuming *α* = 0.05 and a (?) power = 80, 87 patients are needed for both groups. The effect size is 0.54. Assuming a 10% patient drop-out rate during the 30-day follow-up period, a total of 192 patients, i.e., 96 in each group, is needed.

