### Statistical methods

The findings will be analyzed using SPSS (version 27 or higher) (IBM Corp., Armonk, NY, USA) for Windows. Both intention-to-treat and per-protocol analyses will be performed.

Between-group comparisons of continuous variables will be performed using Student’s *t* test or with the Mann–Whitney *U* test if heterogeneous variances persist. Categorical data will be compared using the *χ*^2^ test or Fisher’s exact test. Long-term survival will be analyzed using Cox regression or Kaplan–Meier’s analysis. Two-tailed *p* values will be reported. *P*-values ≤ 0.05 are considered significant. If data for a certain variable is missing the case will be removed from the analysis in question.

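### The only stated comparison for the primary CCI is an unadjusted two-sample test, although predictors of morbidity are recorded before surgery; it is valid but gives up precision

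*Protocol article*

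**What the plan says.** Under Outcomes, the article states: "The main endpoint of the study will be 30-day postoperative morbidity, which will be evaluated from the Comprehensive Complication Index (CCI) of all patients". The index runs from 0 to 100.

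Under Pre-intervention data, it lists "Age, sex, BMI, ASA classification, co-morbidity according to the Charlson comorbidity index", together with a yes/no item for preoperative ICU need. The schedule of events (Table 2) places demographics, medical history and preoperative ICU need at baseline.

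Under Statistical methods: "Between-group comparisons of continuous variables will be performed using Student’s" t test, with Mann-Whitney as the alternative when variances are unequal. The CCI is not named there, but no other method is given for a continuous score. The only regression mentioned is Cox, for long-term survival. The same section says "Two-tailed *p* values will be reported" and removes a case from any analysis for which a variable is missing.

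Under Allocation, there are separate randomisation lists by centre and by indication (obstruction, perforation, other). Neither factor enters the stated analysis.

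**The concern.** Age, ASA class, Charlson index and preoperative need for intensive care are plausible predictors of complications after emergency resection, and the eligible population is broad. None of them is a randomisation factor. Comparing the CCI without them leaves any variance they explain in the error term, which widens the confidence interval and lowers power.

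The article itself describes recruitment in emergency settings as challenging, so precision is easier to gain from the analysis than from more patients. Timing matters too. Outcome assessment is largely unblinded, all authors may see the data, and a preliminary analysis is planned at 50 patients per group (Data monitoring). A covariate list chosen after that point could look data-driven.

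**Working it through.** **1. The plan's own figure.** Inputs from Sample size: "report 48.3% 30-day postoperative morbidity after open surgery and 27.8% after laparoscopy" and "0.05 and a (?) power = 80, 87 patients are needed for both groups". Two-sided, pooled, no continuity correction, with mean rate 0.3805 and difference 0.205:

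n = [1.960·√(2·0.3805·0.6195) + 0.842·√(0.483·0.517 + 0.278·0.722)]² / 0.205² = (1.346 + 0.565)² / 0.0420 ≈ 87 per group.

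The 87 reproduces, but as an unadjusted comparison of two proportions. No CCI mean or SD is given. The statement "The effect size is 0.54" does not fill that gap: a standardised difference of 0.54 would need 2·(2.802/0.54)² ≈ 54 per group, not 87.

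**2. What adjustment could add.** If baseline covariates explain a share R2 of the outcome variance, the residual SD is multiplied by √(1 − R2). Starting from a generic 80% unadjusted power:

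power = Φ[(1.960 + 0.842)/√(1 − R2) − 1.960]; equivalent unadjusted n = 87/(1 − R2).

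| R2 (assumed) | CI width factor | Power | Equivalent n per group |
|---|---|---|---|
| 0 | 1.000 | 80% | 87 |
| 0.05 | 0.975 | 82.0% | 91.6 |
| 0.10 | 0.949 | 84.0% | 96.7 |
| 0.20 | 0.894 | 87.9% | 108.8 |

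**3. Which adjusted method.** If the planning rates count any complication, 100 − 48.3 = 51.7% of open and 100 − 27.8 = 72.2% of laparoscopic patients would score zero. A simulation with assumed shapes used 87 per arm and 6,000 replicates. Occurrence followed those rates, severity was skewed, there was one normal covariate, and treatment affected occurrence only. Power was:

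| R2 | t test | Linear ANCOVA | Mann-Whitney | ANCOVA on ranks |
|---|---|---|---|---|
| 0.006 (no true effect of the covariate) | 65.9% | 65.3% | 77.1% | 77.2% |
| 0.07 | 61.7% | 64.4% | 75.0% | 77.7% |
| 0.20 | 54.1% | 63.4% | 71.4% | 80.8% |

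Rows should be read across, since a stronger covariate also widens the spread of the score. At R2 of 0.20, adjustment adds about 9 points on either scale (54.1 to 63.4; 71.4 to 80.8). Linear ANCOVA on the raw score nevertheless stays below unadjusted Mann-Whitney in every row. Type I error was 4.6% to 5.0% for all four tests. A covariate with no prognostic value cost nothing material.

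**4. Missing covariates.** If the case-removal rule drops a fraction m of patients, the equivalent n is 87·(1 − m)/(1 − R2). At m = R2 the gain is gone: with both at 0.05, 87·0.95/0.95 = 87.

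**The case against.** The strongest reply is that nothing here is wrong. An unadjusted comparison of randomised arms is valid, the Statistical methods paragraph is generic, and a covariate list could sit in an analysis plan that is not shown. The first part stands: this is lost efficiency, not an error. The last part stands only partly. The article does not leave the method open. It names the tests for continuous outcomes, and an adjusted primary analysis elsewhere would depart from that published text.

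A reader might infer that chance imbalance in frail patients biases the result. It does not: the unadjusted standard error and type I error already allow for it.

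A reader might also infer that a linear model on the raw CCI with these covariates is the obvious improvement. With many zeros and an effect on occurrence only, it did worse than the Mann-Whitney test the article already allows. In a further check that added an effect on severity, the linear model was about level with Mann-Whitney at R2 of 0.05 to 0.10 and ahead at about 0.20 (84% against 80%). The ranking therefore depends on the shape assumed.

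Two smaller points stand. Patients must be competent to consent, so preoperative ICU need may be rare and explain little. Indication may correlate with ASA class and ICU need, so adjusting for indication alone would recover some of the variance.

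**Conclusion.** The point holds as a recommendation. The article collects prognostic baseline data and states an unadjusted test for a continuous score such as its primary endpoint. Prespecified adjustment is a better use of the same data, provided the method suits the score's distribution.

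The size is conditional. An R2 of 0.05 to 0.20 would lift a generic 80% power to about 82% to 88%, or narrow the interval by about 2.5% to 10.6%. It is tempting to read this as the power the trial would have. The documents do not support that: the stated 80% belongs to a two-proportion calculation, power on the CCI was never established, and neither R2 nor a CCI standard deviation is given. Nor is adjustment free under the present wording, because the case-removal rule could cancel the gain. The simulation results rest on assumed shapes; they guide the choice of method and are not forecasts.

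**What to change.** In Statistical methods, name the primary CCI comparison as a prespecified covariate-adjusted analysis suited to a skewed score with many zeros: ANCOVA on ranks, or a proportional-odds model on the ordered CCI.

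- **Terms:** randomised arm; age, ASA class and Charlson index; preoperative ICU need if it is not too rare; and the randomisation factors centre and indication.
- **Timing:** fix the list before any comparison by arm, including the preliminary analysis at 50 per group. The article reports 75 enrolled, so this should be done promptly.
- **Exclusions:** no variable recorded at operation, such as contamination, because it is observed after allocation.
- **Missing covariates:** exempt baseline covariates from the case-removal rule and use simple imputation, so that no randomised patient leaves the primary analysis for this reason.
- **Supporting result:** report the unadjusted comparison alongside.

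The data are already on the case report form, so only wording changes. The cost in degrees of freedom is small: 5 for six centres, 2 for three indications and, at one each, 4 for the remaining covariates, 11 in all against 2 × 87 = 174 patients. The adjusted effect measure is not a simple mean difference, and the supporting unadjusted result covers that.

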### Intervention data

The surgical technique (open/laparoscopic/conversion) and type of resection using the Nordic Medico-Statistical Committee (NOMESCO) Surgical Procedural codesAnastomosis (intra- or extracorporeal, hand-sewn or stapled) or/and ostomy (loop-ileo-or colostomy or end ileo-or colostomy). Was the anastomosis tested intraoperatively (air–water leak test/endoscopy)?Contamination (preoperative/perforation/abscess/local peritonitis/general peritonitis)Duration of operation (min), duration of anesthesia (min), blood loss (ml), blood transfusion (IU), intraoperative fluids (ml), and the need for vasoactive drugs (noradrenaline) during the operation (yes/no)

### Post-intervention data

Need for ICU treatment (days), need for nasogastric tube (days), flatus (days), first bowel movement (days)Pain medication: epidural anesthesia (days), need for opioids (days), pain medication at dischargeLOS, discharge to home or to rehabilitation unitAll complications described and measured by the Clavien-Dindo classificationDemand for re-operationThe GIQLI questionnaire (points) 90 days postoperativelyFor oncologic patients: OS, CSS, DFS, adjuvant therapy (days)Follow-up at 6 months, 1, 3 and 5 yearsIn the case of metastatic disease: OS, CSS, chemotherapy (days)If remission is achieved (days)- > DFS

### Participant timeline

Recruitment of patients started in September 2021 at Päijät-Häme Central Hospital and will last for 3–4 years. The estimated enrolment schedule is presented in Table 1. The progress of enrolment is expected to vary between participating hospitals because of differences in the annual caseloads of emergency colorectal diseases. The endpoint of the study is when the final patient recruited reaches the 90-day follow-up and for the oncologic assessment when the final patient recruited reaches the 5-year follow-up or dies.

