#### Permanent ostomy

Permanent ostomy (yes/no) is defined as no stoma reversal within 2 years of the operation, as nearly all reversals are performed within that timeframe [26].

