### Data management

All data will be handled with the utmost confidentiality. Patients’ CRFs will be filled in by the study personnel during postoperative monitoring. The data will then be entered manually in the electronic database (SPSS). All patients will be supplied with a research number and the keyfile connecting research number with patient identification number stored separately from the main dataset. Both files will be placed into locked storage, accessed only by research personnel on faculty computers accessed only with a personal password. At the end of the study period, all data will be destroyed. Permission for the study register has been given by the ethics committee of Helsinki University Hospital and by the Päijät-Häme Central Hospital administration.

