## Data Availability

[name] and [name] have access to the final trial dataset. There are no contractual agreements limiting such access for investigators.

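### The stated study end does not cover the 2-year ostomy endpoint in non-cancer patients, and the survival endpoints are timed from first cancer treatment rather than randomisation

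*Protocol article*

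**What the plan says.** **Study end.** The Participant timeline section of the protocol article says "The endpoint of the study is when the final patient recruited reaches the 90-day follow-up" and adds a second end "for the oncologic assessment when the final patient recruited reaches the 5-year follow-up or dies". No third end is given.

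**Ostomy.** Under Outcomes, "Permanent ostomy (yes/no) is defined as no stoma reversal within 2 years of the operation". The definition stands among the general secondary endpoints, ahead of the block headed for oncologic patients. In Table 2 (the schedule of events) the ostomy-closure row is marked in the 2-year column and carries no restriction to cancer patients.

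**Survival endpoints.** "OS is defined as the time (years) from initial cancer treatment to death for any reason". CSS and DFS use the same starting point. The exclusion criteria cover trauma, acute pancreatitis, reoperation for a complication of an earlier procedure, and ruptured aortic aneurysm. A cancer that has already been treated is not on the list.

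**Data destruction.** The Data management section says "At the end of the study period, all data will be destroyed". It does not say which of the two ends is meant.

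**The concern.** There are two faults of timing.

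First, an endpoint that takes 2 years to observe cannot be complete in a patient whose study participation closes earlier. The definition makes this worse than ordinary missing data, because permanent ostomy is the absence of a reversal. If follow-up stops early, a stoma that has not yet been reversed is either wrongly counted as permanent or left out under the rule in Statistical methods that removes cases with missing values. In either case the comparison rests on something other than the defined endpoint.

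Second, a randomised comparison of survival should start when patients are randomised. If the clock starts at an earlier treatment, the interval up to randomisation is time the patient must have survived in order to be enrolled. For DFS, a patient enrolled with a recurrence had the event before the surgical approach was assigned. This matters because the Objectives section states a superiority hypothesis for oncologic patients, and the Discussion treats the oncologic outcome as a distinguishing feature of the trial.

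**Working it through.** The plan gives no calculated figure on this point, so there is none to reproduce. The check is calendar arithmetic and a side-by-side reading.

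**Inputs**
- Expected end of recruitment: 30 September 2025 (Trial status).
- General study end: last patient + 90 days (Participant timeline).
- Oncologic end: last patient + 5 years, or death (Participant timeline).
- Ostomy window: 2 years from operation (Permanent ostomy; Table 2).
- Visit window at 90 days: +60 days (Table 2).
- Assumption: the last patient is operated on at the end of recruitment. Surgery falls within 48 h of the decision to operate, so the error is at most days.

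**Dates**

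| Milestone | Calculation | Date |
|---|---|---|
| General study end | 30 Sep 2025 + 90 days | 29 Dec 2025 |
| Same, with the +60-day window | 30 Sep 2025 + 150 days | 27 Feb 2026 |
| Last 2-year ostomy status | 30 Sep 2025 + 2 years | 30 Sep 2027 |
| Oncologic end | 30 Sep 2025 + 5 years | 30 Sep 2030 |

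Gap between the general end and the last ostomy status: 730 − 90 = 640 days, about 21 months. With the window it is 730 − 150 = 580 days, about 19 months. The gap does not depend on when recruitment actually ends.

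Latest operation date with 2 years complete at the general end: 29 Dec 2025 − 2 years = 29 Dec 2023. Patients operated on up to then are covered, because the 90 days are counted from the last patient. Later non-cancer patients are not. Cancer patients remain under follow-up to 5 years, so their 2-year status can be obtained.

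The Post-intervention data section does not close the gap. Its follow-up times of 6 months and 1, 3 and 5 years stand with the oncologic items; it names no 2-year contact and does not list stoma reversal.

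**Survival origin.** Let D be the time from first cancer treatment to randomisation and T the time from randomisation to death.
- The defined OS is D + T; a randomised comparison needs T.
- If the emergency resection is the first treatment, D is close to zero and the two agree.
- If the patient was treated before, for example with chemotherapy, or presents with an obstructing recurrence, D is positive and death during D was impossible by selection. Kaplan–Meier or Cox analysis on D + T, without allowance for late entry, counts that patient as at risk throughout D.
- For DFS, if recurrence came at R with R < D, the event precedes randomisation and the surgical approach cannot have influenced it.

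The protocol gives neither the number of such patients nor any value of D, so no numerical effect can be calculated.

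**The case against.** **The ostomy endpoint is planned.** It is defined, and Table 2 schedules it for everyone. Staff who follow the schedule will collect it, and the only defect is a sentence that omits a milestone. This stands as far as it goes: loss of data follows only if the Participant timeline sentence is applied. But the two statements cannot both hold for late non-cancer patients, and the study end is a stated rule.

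**The survival origin is harmless.** For a cancer that first presents as an emergency, the index resection is likely to be the first treatment. The exclusion of reoperations narrows the pre-treated group. Any earlier interval is fixed before randomisation and should balance between arms on average. All of this stands, and it is why no bias in favour of either arm is claimed. It does not rescue the definition: absolute survival would still be overstated for pre-treated patients, and a DFS event before randomisation still makes no sense.

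**Stronger readings that the document does not support**
- *Data are destroyed at 90 days, before ostomy status exists.* A reader might infer this, but the Data management section names no 90-day trigger. With an oncologic end in 2030, later destruction is the natural reading, and by then the 2-year status exists. What remains is an ambiguity.
- *Destruction contradicts the Data Availability section.* That section only names who "have access to the final trial dataset". Access now and destruction later are compatible.
- *About 60% of non-cancer patients are affected.* The figure comes from (192 − 75)/192 = 61% still to be enrolled, but the count of 75 is undated. Uniform accrual from an assumed 1 September 2021 gives a different answer: 849 of 1,490 days (57%) fall before 29 December 2023, leaving 43%. Neither figure speaks to non-cancer patients or to those given a stoma, whose numbers are not stated.
- *DFS is analysed only in metastatic patients who reach remission.* The words "If remission is achieved (days" stand in a list of data items. They do not define an analysis set, and the DFS definition carries no such condition.

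**Conclusion.** The point holds in two parts.

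1. The Participant timeline section conflicts with the ostomy definition and with Table 2. The stated end falls about 21 months (19 with the visit window) before the last non-cancer patient's ostomy status is due. Non-cancer patients operated on after 29 December 2023 would lack it if that section were followed. The cut-off date rests on recruitment ending as expected on 30 September 2025. How many patients are affected cannot be derived.

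2. OS, CSS and DFS have the wrong origin for a randomised comparison, because previously treated cancer is eligible. The effect is probably small, on the assumption that the emergency resection is the first treatment for most cancer patients. It is a definition to correct, not a demonstrated bias.

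The end that triggers data destruction also needs to be named. The 30-day primary endpoint is unaffected by any of this.

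**What to change.** - **Participant timeline:** add that, for ostomy status, the study ends when the last patient reaches 2 years after the operation.
- **Overall, cancer-specific and disease-free survival:** start all three at randomisation for every oncologic patient.
- **Data management:** state that destruction follows the last (5-year) follow-up and its analysis.

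The cost is protocol wording and notification of the ethics committee. The 2-year ostomy check is already in Table 2, and randomisation dates should be on record, so no new visit or data item is needed. No sample-size figure changes. Vital status at 2 years in non-cancer patients need not be added: Table 2 schedules mortality at 90 days, and the ostomy endpoint as defined does not call for it.

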### Objectives

The objective of this study is to evaluate whether patients benefit from the laparoscopic approach in emergency colorectal surgery, whether benign or malignant disease.

Our hypothesis is that the same beneficial effects of laparoscopy seen in elective surgery and in other entities needing emergency surgery will also apply to emergency colorectal surgery. These benefits are lower overall postoperative morbidity, shorter in-hospital stay, less postoperative ileus, less postoperative pain, fewer wound complications, and lower risk of mortality.

For oncologic patients, our hypothesis is that the laparoscopic approach is superior to the open approach, partly because of the faster recovery associated with greater access to oncologic treatment and partly because in laparoscopy the intra-operative circumstances need to be optimized to mimic the elective situation, leading to good visualization and a standardized approach.

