#### Exclusion criteria

The patient’s condition is due to traumaSimultaneous acute pancreatitisThe need for resection is due to a complication from a previous procedure, i.e., reoperationSimultaneous ruptured aortic aneurysm or ruptured aortic aneurysm as the underlying cause of the need for surgery

All patients arriving in the emergency room and diagnosed with a condition requiring emergency colorectal resection will be considered for inclusion. After receiving proper information on the possible advantages and disadvantages of the intervention, and after voluntarily signing the informed consent form, the subjects will be enrolled in the trial. The written consent will be obtained by a member of the research group and a copy given to the patient. After enrolment, the patient will be randomized for either open or laparoscopic surgery. The procedure will be carried out or closely supervised by a specialist in gastrointestinal surgery experienced in colorectal resections. Patients considered but not meeting the inclusion criteria and patients with at least one exclusion criterion will not be enrolled. These patients and the reasons for their exclusion will be documented. Postoperative care and follow-up will follow normal praxis and the case report form will be completed. Ninety days after surgery, patients will be requested to fill in the Gastrointestinal Quality of Life Index (GIQLI) questionnaire, which is the only deviation from normal follow-up. The GIQLI questionnaire will be sent by post at no cost to the patient. Once enrolled, patients will not be required to make any further visits to the hospital or to undergo any radiation or medical procedures. The follow-up for oncology patients will also be arranged according to the normal follow-up schedule.

If at any point the allocated type of intervention needs to be modified or even discontinued because of patient safety or for any other reason, the circumstances and reasons will be carefully documented and the patient will be informed. For example, if the patient’s condition changes, making the patient unfit for surgery, the patient will normally be excluded. In the event of conversion during the operation, the circumstances will be carefully documented but the patient will still be able to participate.

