### Recruitment

All subjects fulfilling the inclusion criteria will be considered for participation in the trial. An anonymous record will be kept prospectively for all subjects fulfilling the inclusion criteria but not attending, either for not consenting or for any other reason, for later assessment of selection bias. The schedule of events in the study is shown in the Table 2.

**Table 2 Tab2:** SPIRIT figure

Schedule of events	Baseline	Procedure	Postoperative monitoring during hospital stay	Discharge	30 days	90 (+ 60) days	1 years	2 years	3 years	5 years	Unscheduled visit
Informed consent	X										
Need for preoperative intensive care/intensive care unit treatment	X										
Demographics and medical history	X										
Procedure details		X									
Need for postoperative intensive care/intensive care unit treatment			X								
Bowel function			X								
Analgesics			X	X							
Complications		X	X	X	X						
Gastrointestinal Quality of Life Index (GIQLI)						X					
Mortality						X					
Oncological patients: TNM classification, adjuvant chemotherapy, chemotherapy OS, CSS, DFS							X		X	X	X
Ostomy closure								X			
Protocol deviation	X	X	X	X	X		X		X	X	X

*OS* overall survival, *CSS* cancer-specific survival, *DFS* disease-free survival

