## Trial status

Approval by the Ethics Committee of Helsinki University Hospital was received (reference1106/2021), and patient recruitment at Päijät-Häme Central Hospital started in September 2021. So far, 75 patients have been enrolled. Other hospitals started recruitment during 2023. Recruitment is expected to end on 30 September 2025. This is version 1 of the protocol.

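### As worded, the death of the last recruited patient would close the oncologic assessment before other cancer patients reach their scheduled 5-year visit

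*Protocol article*

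**What the plan says.** Participant timeline gives two closing rules in one sentence. For the trial as a whole: "The endpoint of the study is when the final patient recruited reaches the 90-day follow-up". For the cancer part: "for the oncologic assessment when the final patient recruited reaches the 5-year follow-up or dies". Both refer to a single person, the last recruit, but only the second adds death as an alternative trigger.

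Elsewhere, follow-up is set for each patient. Post-intervention data lists oncologic follow-up at six months and at one, three and five years. Table 2 (under Recruitment) has the row "Oncological patients: TNM classification, adjuvant chemotherapy, chemotherapy OS, CSS, DFS", marked at years 1, 3 and 5. The text after the exclusion criteria adds: "The follow-up for oncology patients will also be arranged according to the normal follow-up schedule".

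Three further statements bear on the point. The Objectives cover patients "whether benign or malignant disease". Recruitment began in September 2021 and "will last for 3–4 years"; Trial status says "Recruitment is expected to end on 30 September 2025". Data management says "At the end of the study period, all data will be destroyed".

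**The concern.** A closing date set by the last recruit works when it is a fixed interval after that person's entry, because everyone who entered earlier has then been observed for at least as long. Making that person's death a second trigger removes the guarantee. If the last recruit dies early, patients who entered in the preceding years are still alive and under observation, but the assessment is over.

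Overall, cancer-specific and disease-free survival are secondary endpoints, and the Discussion presents oncologic outcome as a distinctive strength of this trial. How long these endpoints are observed should not depend on whether one emergency patient survives. That patient may not even belong to the oncologic cohort, since the sentence speaks of the last patient recruited and the trial admits benign disease.

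**Working it through.** The plan gives no figure on this point to reproduce. Its one calculated figure, 87 patients per group, does reproduce (48.3% v 27.8%, two-sided 0.05, power 80%, no continuity correction) but plays no part here.

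**Inputs from the article.** Recruitment length R: three to four years (Participant timeline); September 2021 to 30 September 2025 is about four. Target visit: five years (Post-intervention data, Table 2). Closing rule: last recruit at five years or dead (Participant timeline).

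**Assumptions.** Accrual is uniform over R, oncologic patients accrue like the rest, and the 5-year clock starts close to recruitment. The time t from the last recruitment to that patient's death is varied, because the article gives no mortality rate.

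**Formula.** A patient who entered r years before the last recruit has potential follow-up min(5, t + r). Five years is possible only if r ≥ 5 − t. With r uniform on 0 to R, the share able to reach five years is max(0, (R − (5 − t))/R).

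| Last recruit dies at year t | Must have entered at least this long before | Share, R = 4 | Share, R = 3 |
|---|---|---|---|
| 1 | 4 years | (4 − 4)/4 = 0% | 0% |
| 2 | 3 years | (4 − 3)/4 = 25% | (3 − 3)/3 = 0% |
| 3 | 2 years | (4 − 2)/4 = 50% | (3 − 2)/3 = 33% |
| 4 | 1 year | (4 − 1)/4 = 75% | (3 − 1)/3 = 67% |
| survives 5 years | – | 100% | 100% |

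These are shares that could be observed to five years if alive, not shares surviving.

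For a very early death, t = 0.25, the longest possible follow-up is R + t: 4.25 years (R = 4) or 3.25 years (R = 3), so nobody reaches the 5-year visit.

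The 3-year visit is hit less hard. With R = 4 the share is (4 − (3 − t))/4: 50% at t = 1, 75% at t = 2 and 100% from t = 3.

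**Sensitivity to accrual.** Slower early accrual lowers the shares. Trial status reports 75 patients enrolled without dating the count. If those 75 are assumed to have entered evenly over 2.5 years (30 a year) out of 192 in a four-year recruitment, a death at year 2 leaves 30/192 = 16% and at year 3 leaves 60/192 = 31%. The 2.5 years is an assumption.

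**Without the death trigger.** Closing only once every oncologic patient has had the chance of five years gives 100% in every row. With recruitment ending on 30 September 2025, that is September 2030 at the latest.

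**The case against.** The strongest reply is that the sentence is shorthand. It follows the last-patient-last-visit convention, and the death clause says only that someone who has died cannot attend a 5-year visit. No section says that data collection on other patients stops at that death. The visit schedule, Table 2 and the statement on normal oncology follow-up all point to five years for each patient. This is probably what was meant, and it stands as a reading of intent. It does not mend the text: the sentence defines when the assessment ends, and to carry the intended meaning it must refer to all oncologic patients, not the last recruit.

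Several stronger readings are tempting and are not supported:

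- **That one death stops follow-up for everyone, in flat contradiction of Table 2.** Only the last recruit's death counts; anyone who entered at least 5 − t years earlier is unaffected; and there is no conflict if that patient survives five years. Clinical follow-up would continue under normal practice in any case.
- **That the early stop is likely.** Any trigger probability would only restate an assumed survival rate, and the article supplies none.
- **That the survival analyses would fail.** The endpoints are defined as times to event with no 5-year landmark and are to be analysed by Cox regression or Kaplan–Meier. Earlier administrative closure costs late follow-up and precision, not validity.
- **That the data would then be destroyed.** Data management ties destruction to the end of the study period but does not link that term to the closing rule. The sequence is an inference.
- **That the loss falls mainly on newly opened centres.** Trial status says only that the other hospitals began recruiting during 2023, and the enrolment table is not shown.

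**Conclusion.** The closing rule for the oncologic assessment is wrong as written, with a conditional consequence. If the last recruited patient dies before five years, the assessment closes before later-recruited oncologic patients reach a visit that the article itself schedules. Under four-year recruitment and uniform accrual, both working assumptions, the share able to reach five years falls from 100% to 0%, 25% or 50% for a death at year 1, 2 or 3; with three-year recruitment it is 0%, 0% or 33%. How probable such a death is cannot be stated from the article. What is at risk is length of follow-up and precision for three secondary survival endpoints. The 30-day primary endpoint and the sample size are not affected. The point is worth correcting because the wording matters and the remedy is trivial, not because the design is unsound.

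**What to change.** In Participant timeline, replace the oncologic closing rule with: the oncologic assessment ends when every oncologic patient has died, been lost to follow-up, or completed the 5-year follow-up. This makes death an end of that patient's own follow-up and removes any dependence on a last recruit who may have benign disease.

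Do not gloss the new rule as five years after the last oncologic patient was randomised. The two dates can differ when that patient dies early, and the survival endpoints are counted from initial cancer treatment, not randomisation.

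In Data management, state that the end of the study period, on which destruction of the data depends, is not earlier than the date set by this rule.

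The cost is two sentences. No visit is added, since the follow-up is already scheduled under Post-intervention data and in Table 2 and runs alongside normal oncology care.
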